## Abstract

**Objectives:**

It remains unclear whether the modified nutrition protocol for critically ill patients (mNEED), based on the NOFI predictive model for feeding intolerance (FI), can reduce the incidence of FI and subsequently improve clinical outcomes.

**Design:**

This is a multicenter, cluster-randomized controlled trial.

**Setting:**

Ninety intensive care units (ICUs) across China.

**Participants:**

A total of 2,250 critically ill patients initiating early enteral nutrition who meet the inclusion criteria.

**Intervention:**

In addition to standard care, centers randomized to the intervention arm will implement nutritional therapy strictly according to the mNEED protocol.

**Primary outcome measure:**

The primary outcome is the incidence of FI within the first 7 days of ICU admission. Secondary outcomes and process measures will also be reported. An intention-to-treat analysis will be conducted for the primary outcome to ensure the robustness of the findings.

**Ethics and dissemination:**

This study has been approved by the Ethics Committee of the First Hospital of Jilin University (original version: 24k004-001; revised version: 24k004-002) and by the ethics committees of all participating sites. Results will be disseminated through peer-reviewed publications and conference presentations.

**Trial registration:**

This trial has been registered at the Chinese Clinical Trial Registry (ChiCTR2400081581): https://www.chictr.org.cn/showproj.html?proj=219477 and at ClinicalTrials.gov (NCT06827275): https://clinicaltrials.gov/study/NCT06827275.

## Introduction

1 

Nutritional support is critically important for patients in the intensive care unit (ICU). Major international evidence-based guidelines consistently recommend the provision of early, targeted nutritional therapy for critically ill patients (1, 2). However, cluster randomized controlled trials (cRCTs) evaluating the impact of guideline implementation on early targeted nutrition have not demonstrated patient benefit (3, 4). In 2022, Ke et al. proposed the Nutrition Evidence-based feeding guidelines for critically ill patients (NEED), which offer a specific feeding protocol for nutritional therapy in critical illness (4). The results suggested that the NEED group initiated enteral nutrition (EN) earlier and had reduced overall parenteral nutrition (PN) use.

Nevertheless, analysis of the study data revealed that the mean time to EN initiation in the NEED group was 1.2 days, and only about 60% of patients achieved 70% of target energy via EN within 72 h. The remaining 40% of patients met the definition of feeding intolerance (FI) (5). Notably, this study did not report the incidence of gastrointestinal (GI) complications such as diarrhea or gastric retention. Given the substantial number of patients with suboptimal EN delivery, it can be inferred that nearly half of the patients in the NEED group may have met the diagnostic criteria for FI, with no significant difference compared to the control group. This may indicate that the NEED protocol did not reduce—and may have even increased—the incidence of FI. In the acute phase of critical illness, the occurrence of FI is often one of the most clinically concerning events for ICU physicians.

Feeding intolerance may result in feeding interruption or delay, thereby hindering the successful implementation of EN and its associated benefits. This can lead to delayed energy target achievement, development of malnutrition (6), prolonged hospital stays (7), and even increased mortality (8, 9). Studies have shown that persistent FI during the first week of ICU admission is an independent risk factor for 28-day and 90-day mortality (9). Therefore, optimizing feeding strategies to reduce the occurrence of FI holds significant clinical importance.

In our previous study, we developed a predictive model for FI in critically ill patients—NOFI—which incorporates primary diagnosis, the Acute Physiology and Chronic Health Evaluation II (APACHE II) score, and Acute Gastrointestinal Injury (AGI) grade to predict the individual risk of FI (10). This model demonstrated good discrimination, calibration, and clinical utility. Based on this model, we aim to modify the NEED protocol (modified NEED, or mNEED) to reduce the occurrence of FI while still meeting the nutritional needs of critically ill patients.

The objective of this study is to evaluate the impact of the NOFI-based modified NEED protocol on patient outcomes. A cluster-randomized design will be adopted, in which participating ICUs will be randomly assigned to either the mNEED group or the standard guideline-based group. We hypothesize that the mNEED protocol may reduce the incidence of FI and potentially improve the prognosis of critically ill patients compared to standard guideline-based care.

## Methods and analysis

2 

### Study design

2.1 

This is a multicenter cluster randomized controlled trial conducted by the Chinese Critical Care Nutrition Trials Group (ChiCTR2400081581^1^; NCT06827275^2^). The trial protocol was developed in accordance with the Standard Protocol Items: Recommendations for Interventional Trials (SPIRIT) statement (11). The final version of the plan is 5.0, with the date being 16 December 2024.

### Study population

2.2 

All patients will be screened consecutively during routine clinical care: every individual admitted to the participating hospitals’ ICUs will be evaluated for eligibility. Enrollment in the trial will proceed only after written informed consent has been obtained from the patient or a legally authorized representative.

#### Inclusion criteria (for patients)

2.2.1 

Aged ≥ 18 years;Presence of one or more organ system failures within 24 h of ICU admission (SOFA score ≥ 2);Expected ICU stay > 48 h;Inability to take oral nutrition;No contraindications to enteral nutrition (EN).

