#### Randomization

2.4.1 

This study employed a multicenter, stratified block-randomized controlled trial with cluster allocation at the ICUs level. A total of 108 ICUs were enrolled, including 102 tertiary general hospital ICUs and 6 other-level ICUs, as of 15 June 2025. Stratified randomization was performed by first stratifying ICUs according to their level (tertiary general hospital/others), followed by generating block randomization sequences within each stratum using R software (version 4.4.1). Clusters were allocated in a 1:1 ratio to either the intervention group or control group. Finally, 54 ICUs were assigned to each group. Due to the nature of the intervention, a partial blinding approach was adopted: participating patients, center implementers, and outcome assessors were aware of group allocation, while members of the endpoint adjudication committee remained blinded to allocation status.

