#### Blinding

2.4.2 

Participants or their legal representatives will be completely blinded to group allocation. Healthcare providers will only be aware of the feeding protocol used in their own center and will not be informed of group assignments in other centers. Outcome assessments will be conducted by a dedicated research team that is not involved in the implementation of the feeding protocols and is unaware of the grouping of these patients. For the primary outcome, after the study is completed, GI symptoms and daily feeding data recorded in the database will be reviewed and consolidated by the research team at the coordinating center to perform a unified evaluation. Statistical analyses will also be conducted by researchers at the coordinating center. Emergency unblinding will be permitted in cases of safety concerns or when significant differences in outcomes between groups are observed.

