#### Interventional arms

2.4.3 

According to the randomization scheme, all centers will be assigned to either the intervention group or the control group in a 1:1 ratio before patient recruitment begins. Table 1 shows the schedule of enrollment, interventions, and assessments based on the SPIRIT 2013 statement (11). Detailed reporting checklists are provided in the Supplementary Table 1 (SPIRIT 2013 checklist) and Supplementary Table 2 (CONSORT–Cluster checklist) (12).

**TABLE 1 T1:** Schedule of enrollment, interventions, and assessments.

	Study period						
	Enrollment	Allocation	Post-allocation				Close-out
Timepoint	0–48 h	0–48 h	Day 1	Day 7	Day 28	Day 90	T_*E*_
Enrollment:							
Eligibility screen	X	–	–	–	–	–	–
Informed consent	X	–	–	–	–	–	–
Allocation	–	X	–	–	–	–	–
Interventions:	–	–	↔			–	–
(mNEED group)	–	–	↔			–	–
(Control group)	–	–	–	–	–	–	–
Assessments:	–	–	–	–	–	–	–
(Baseline characteristics)	X	X	–	–	–	–	–
(Muscle ultrasound assessment)	–	–	X	–	X	–	–
(Laboratory tests)	–	–	↔			–	–
(Therapies and medication use)	–	–	↔			–	–
(Critical illness and nutrition-related scores)	–	–	↔			–	–
(Nutrition delivery)	–	–	↔			–	–
(Gastrointestinal symptoms]	–	–	↔			–	–
(Rehabilitation therapy)	–	–	↔			–	–
(Clinical outcomes)	–	–	↔				–
(SF-36 and EQ-5D-5L)	–	–	–	–	X	X	
(Adverse events)	–	–	–	–	–	–	X

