##### Arm#1 mNEED group

2.4.3.1 

If a center is randomized to the intervention group, training on the implementation of the mNEED nutrition protocol and ultrasound assessment will be conducted before enrolling the first patient. The mNEED protocol includes several modifications to the original NEED protocol:

For patients with AGI ≤ III, the risk of feeding intolerance (FI) is predicted using the NOFI model. Based on the predicted probabilities (< 30%, 30%–85%, and > 85%), different feeding strategies are adopted according to the threshold values identified from the NOFI decision curve analysis.The initial feeding rates have been reduced overall. Instead of the original rates of 25 mL/h for AGI < I and 15 mL/h for AGI II–III, the revised rates are: 20 mL/h for < 30% predicted FI risk, 15 mL/h for 30%–50%, and 10 mL/h for 50%–85%.For AGI ≤ III patients with a predicted FI probability > 85%, early EN (EEN) is deferred, and re-evaluation is performed after 12 h.The FI assessment interval has been extended from 4 to 6 h to every 12 h. Additionally, when the FIS (Feeding Intolerance Score) is 0, the incremental feeding volume has been reduced from 10 to 5 mL/h. The rationale for both adjustments is consistent with the overall strategy: to avoid overly rapid feeding advancement during the acute phase, which increases the risk of FI and early overfeeding.A new item has been added to limit energy provision to no more than 70% of the target caloric intake during the first 3 days, in accordance with ESPEN guidelines, to minimize the risk of early overfeeding.The decision to initiate supplemental parenteral nutrition (SPN) is based on evaluating the patient’s nutritional needs curve. The objective is to align nutritional delivery as closely as possible with this curve, ensuring adequate energy provision while avoiding overfeeding.

To monitor whether enrolled patients are managed in accordance with the study protocol, research staff at each participating center are required to complete a feeding record form for every patient until ICU discharge. This form includes detailed components of the FIS, with evaluations performed every 12 h. It records the FIS values and corresponding adjustments in the feeding rate. Upon study completion, electronic versions of the FIS record forms for all patients will be collected via email.

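### Eligibility is decided after the ICU knows its arm, and the wording leaves room for the highest-risk patients to be omitted in mNEED ICUs only

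*Protocol article*

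**What the plan says.** **Order of events.** Section 2.4.3 states that "all centers will be assigned to either the intervention group or the control group in a 1:1 ratio before patient recruitment begins". In the intervention arm, "training on the implementation of the mNEED nutrition protocol and ultrasound assessment will be conducted before enrolling the first patient" (section 2.4.3.1). Patients are screened and give individual consent after that (section 2.2).

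**Who knows the arm.** Section 2.4.1 says "participating patients, center implementers, and outcome assessors were aware of group allocation". Section 2.4.2 says "Participants or their legal representatives will be completely blinded to group allocation". The two sections disagree about patients, but both leave site staff aware of their own centre's feeding protocol. The article mentions no screener who is blind to arm.

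**Who is eligible.** Screening is consecutive: "every individual admitted to the participating hospitals’ ICUs will be evaluated for eligibility" (section 2.2). Section 2.2.1 then requires "No contraindications to enteral nutrition (EN") without saying what counts as a contraindication. The only gastrointestinal exclusion in 2.2.2 is AGI grade IV. The abstract describes the sample as "critically ill patients initiating early enteral nutrition who meet the inclusion criteria", but section 2.2.1 does not require that EN be started early.

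**What only mNEED ICUs do.** For patients with AGI of III or less and predicted FI above 85%, "early EN (EEN) is deferred, and re-evaluation is performed after 12 h" (section 2.4.3.1). Control ICUs have no such rule, and section 2.6.6 counts use of NOFI to guide EN there as contamination.

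**The concern.** An mNEED ICU screens patients with a web tool, a nomogram and a poster that single out some of them for deferral of early EN. Nothing in section 2.2 tells staff whether such a patient still meets the undefined EN criterion, or still belongs to a population that the abstract describes as starting early EN. The enrolment window in Table 1 is 0–48 h and the re-evaluation comes at 12 h, so NOFI can be calculated before eligibility and consent are settled. A control ICU does not face this question, because it does not calculate NOFI.

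If some mNEED sites read the wording as a reason not to enrol, the patients lost are those with the highest predicted risk of the primary outcome, and they are lost from one arm only. FI would then look lower under mNEED with no treatment effect. Consecutive screening ensures that these patients are seen. It does not govern the eligibility decision.

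**Working it through.** **1. The plan's own figure.** Inputs from section 2.3: FI 0.50 against 0.375, two-sided alpha 0.05, power 90%, ICC 0.10, 45 clusters of 25 per arm.
- Two-proportion formula without continuity correction: 329 per arm.
- Design effect: 1 + (25 − 1) × 0.10 = 3.4.
- 329 × 3.4 = 1,118.6 per arm, or about 2,237 in total, against the stated 2,250. The figure reproduces; power at 45 × 25 per arm is 90.2%.
- Effective size used below: 1,125 / 3.4 = 330.9 per arm. Planned difference: 0.50 − 0.375 = 0.125.

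**2. Crude size of one-arm omission.** The documents do not give the share of patients above 85% (f) or their FI rate (r), so both are assumed. If they are omitted from mNEED only and there is no treatment effect:

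apparent mNEED FI = (0.50 − f × r) / (1 − f)

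Example with f = 0.10 and r = 0.90: (0.50 − 0.09) / 0.90 = 0.456. The difference is 0.044, and 0.044 / 0.125 = 36% of the planned difference.

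The false-positive rate is for an unadjusted z-test, with z = difference / √[(0.25 + p(1 − p)) / 330.9], where p is the apparent mNEED FI. Percentages in brackets are shares of the planned 0.125.

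| f | FI at r = 0.85 | FI at r = 0.90 | FI at r = 0.95 | False-positive rate at r = 0.90 (range over r) |
|---|---|---|---|---|
| 5% | 0.482 (15%) | 0.479 (17%) | 0.476 (19%) | 8.4% (7.6–9.4%) |
| 10% | 0.461 (31%) | 0.456 (36%) | 0.450 (40%) | 20.9% (17.1–25.2%) |
| 15% | 0.438 (49%) | 0.429 (56%) | 0.421 (64%) | 44.6% (35.8–53.8%) |

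**3. What the primary model does about it.** NOFI uses primary diagnosis, APACHE II and AGI grade (Introduction). The primary GLMM adjusts for the same three (section 2.7.1). I checked the consequence by simulation:
- 90 ICUs of 25 patients, a logistic model with random ICU intercept (SD 0.6) and no treatment effect.
- Every mNEED patient above 85% risk omitted and replaced.
- 300 runs per setting, with GEE, robust standard errors and 88 degrees of freedom standing in for the GLMM.

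| Share above 85% | Unadjusted OR | Unadjusted rejection | Adjusted OR | Adjusted rejection |
|---|---|---|---|---|
| 4.2% | 0.93 | 9.7% | 0.99 | 6.3% |
| 12.4% | 0.80 | 46.3% | 1.01 | 5.0% |

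Simulation error around 5% is √(0.05 × 0.95 / 300) = 1.3 points, so both adjusted rejection rates are compatible with the nominal level.

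**4. What the simulation assumes.** Omission depended only on the risk score, and the score was measured alike in both arms. It therefore does not cover omission driven by bedside features outside the three predictors, or AGI graded differently by staff who know the arm.

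**The case against.** The strongest case against is that the plan contains no stated conflict, and that the primary analysis already handles the main route of bias.

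Most of the first part stands. A reader might infer that the eligibility criteria contradict the deferral rule. They do not. Early initiation of EN appears in the abstract, not in 2.2.1. The deferral rule applies to patients with AGI of III or less, whom the gastrointestinal exclusion does not remove, and it is presented as a feeding strategy. No section calls a predicted risk above 85% a contraindication. A deferred patient is re-evaluated after 12 h and can still be enrolled within 48 h. A reader might also infer that high-risk patients will be lost from mNEED only. That is possible, not directed. Control staff may also judge very sick patients unsuitable for EN, and mNEED staff, who have a pathway for them, may be readier to enrol them.

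The second part stands for selection on NOFI alone, as the simulation shows. It does not cover selection on unmeasured judgement or arm-aware AGI grading. It also leaves unprotected the unadjusted GLMM, which section 2.7.1 lists as a sensitivity analysis.

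On Table 1, the text of 2.4.3 gives the true order, so nothing is concealed. The table still places patient enrolment ahead of allocation, and the two should agree.

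A condensed article may leave a definition of contraindication or a screening log to the full protocol, so their absence is not the point. The point is that the wording shown permits two readings at a moment when the arm is known.

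**Conclusion.** The concern holds as an unresolved ambiguity that permits arm-specific selection after cluster allocation. The omission described would favour mNEED on the primary outcome. Whether it occurs, and how often, cannot be told from the documents.

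The 17%, 36% and 56% figures illustrate an unadjusted analysis under assumed f and r. A reader might take them as the expected bias in the primary result, but the documents do not support that, because the primary GLMM adjusts for exactly the three NOFI predictors. The residual bias in the primary model, through unmeasured judgement or arm-aware AGI grading, is not quantified here. The point merits a change because the repair is cheap and the reporting would show whether the arms differ in baseline risk.

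**What to change.** - **Section 2.2:** state that eligibility is decided and recorded by the same criteria in both arms, before NOFI is calculated and without regard to it. State that patients whose early EN is deferred are enrolled and kept in the intention-to-treat set.
- **Abstract:** reconcile the description of participants with 2.2.1 and the deferral step.
- **Table 1:** show ICU allocation before patient recruitment, as in 2.4.3.
- **Reporting:** have the coordinating centre compute NOFI for all patients in both arms from the recorded diagnosis, APACHE II and AGI grade. Report by arm its distribution, the share above 85%, and the numbers screened, eligible and enrolled.
- **Analysis:** add a sensitivity analysis of the primary endpoint limited to NOFI of 85% or less, so that both arms cover the same risk range.

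Two limits should be stated. The restricted analysis and the NOFI comparison rely on AGI graded at sites that know their arm. Recording eligibility before NOFI does not prevent arm-aware AGI grading, because AGI is already needed for the grade IV exclusion; it only stops the NOFI result from becoming a reason not to enrol.

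The cost is a brief notice to sites and one extra analysis. The NOFI inputs are already needed for the primary model, so the comparison and the restricted analysis remain possible even if recruitment is well advanced.

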#### Exclusion criteria (for patients)

2.2.2 

Received EN therapy within the past 3 days;Grade IV acute gastrointestinal injury (AGI IV);Receiving palliative care with expected death within 48 hours;Pregnancy;Long-term use of corticosteroids or other immunosuppressants;Undergoing radiotherapy or chemotherapy for malignant diseases;Participation in another clinical trial.

#### ICU inclusion and exclusion criteria

2.2.3 

To minimize the impact of inter-institutional differences in medical practice on clinical outcomes, the following criteria were established for participating ICUs.

##### ICU inclusion criteria

2.2.3.1 

ICUs within secondary or tertiary hospitals;ICUs capable of delivering intensive care and monitoring FI;ICU types including emergency, medical, surgical, neurosurgical, or general ICUs.

##### ICU exclusion criteria

2.2.3.2 

ICUs that decline participation;ICUs that fail ethical review approval;Pediatric ICUs.

### Sample size calculation

2.3 

Sample size calculation was performed using PASS software. The primary clinical outcome was the difference in the incidence of FI between the two groups. Based on previous studies, the incidence of FI among critically ill patients in the control group was assumed to be 0.5. According to the clinical decision curve analysis from the predictive model for FI (NOFI) (10), the net benefit at a threshold probability of approximately 50% was 0.257, indicating that around 25.7 patients out of every 100 would benefit from the intervention. Therefore, it was assumed that the mNEED protocol (intervention group) would reduce the incidence of FI by 25%, resulting in an expected FI rate of 0.375 in the intervention group [0.5 × (1–0.25) = 0.375]. We set the intraclass correlation coefficient (ICC) to 0.10 by analogy to the NEED trial (4), a total of 45 clusters per group were planned, with an ICC of 0.1. Using a two-sided alpha of 0.05 and a statistical power of 90% (1–β = 0.9), the required number of participants per cluster was calculated to be 25. Thus, the total sample size was 45 clusters × 25 participants × 2 groups = 2,250 participants. We pre-specified ICC sensitivity analyses, which indicated that the planned configuration is robust to plausible ICC and cluster-size variability; detailed results are provided in Supplementary Tables 3, 4.

### Randomization and study intervention

2.4 

#### Randomization

2.4.1 

This study employed a multicenter, stratified block-randomized controlled trial with cluster allocation at the ICUs level. A total of 108 ICUs were enrolled, including 102 tertiary general hospital ICUs and 6 other-level ICUs, as of 15 June 2025. Stratified randomization was performed by first stratifying ICUs according to their level (tertiary general hospital/others), followed by generating block randomization sequences within each stratum using R software (version 4.4.1). Clusters were allocated in a 1:1 ratio to either the intervention group or control group. Finally, 54 ICUs were assigned to each group. Due to the nature of the intervention, a partial blinding approach was adopted: participating patients, center implementers, and outcome assessors were aware of group allocation, while members of the endpoint adjudication committee remained blinded to allocation status.

